#### Statistical methods

2.6.4

Statistical analyses will be performed on the intention-to-treat (ITT) population and the per-protocol (PP) population. For the ITT analysis, missing data will be handled using multiple imputation by chained equations (MICE). All statistical analyses will be conducted using SPSS software (version 26.0; IBM Corp.). Results will be presented with 95% confidence intervals, and a two-sided *P* value of less than 0.05 will be considered statistically significant. Continuous variables normally distributed will be summarized as mean ± standard deviation, while those with a non-normal distribution will be summarized as median and interquartile range (IQR). Comparisons of continuous variables between the two groups will be performed using the independent samples *t*-test (for normal data) or the Mann–Whitney *U*-test (for non-normal data). Categorical data will be described as frequencies and percentages, and comparisons between groups will be made using the appropriate Chi-squared test or Fisher's exact test. For longitudinal analysis of outcomes measured over time, generalized estimating equations (GEE) or linear mixed-effects models will be employed to account for correlations within subjects and to examine time-by-group interaction effects. In secondary analyses, we will explore potential effect modification by menopausal status by including an interaction term in our statistical models. For the exploratory secondary outcomes, interpretation will focus on effect sizes and confidence intervals rather than unadjusted *P* values to avoid inflation of type I error due to multiple comparisons. No formal multiplicity adjustment will be applied to secondary endpoints.

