#### Primary outcome

2.5.1

The change in urine leakage, as measured by the 1-hour pad test, from baseline to week 6. The test procedure will follow: the participant will wear a pre-weighed pad, drink 500 mL of water within 15 min, and perform a series of activities. These activities include walking for 30 min (which incorporates stair climbing), repeatedly sitting down and standing up, vigorous coughing, running in place, bending to pick up a small object from the floor, and washing hands under running water. The pad will then be reweighed to quantify the urine leakage (21). The assessment will be postponed or rescheduled if the participant is menstruating or experiences an episode of severe coughing.

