#### Sample size calculation

2.6.1

The sample size was calculated for a superiority trial comparing two independent means, with a 1:1 allocation ratio, a two-sided *α* of 0.05 (*Z_α/2_* = 1.96), and a power (1-*β*) of 80%(*Z_β_* = 0.84). Based on data from our previous research, the anticipated change in urine leakage (1-hour pad test) from baseline to week 6 was used for calculation: EA group mean *μ_t_* = 8.59 g, Sham EA group mean *μ_c_* = 4.81 g, standard deviation *σ* = 4.76 g, superiority margin *Δ* = 0. Using these parameters, the calculated sample size required per group was 25. Accounting for an estimated dropout rate of 20%, 64 participants (32 per group) will be required (26, 27).$$n=\frac{2{\left(Z_{\alpha /2}+Z_{\beta }\right)}^{2}\;\times \sigma^{2}}{{\left(\mu_{t}\text{-}\mu_{c}\text{-}\Delta \right)}^{2}}$$

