#### Randomization

2.6.2

According to the enrollment order, eligible participants will be randomly assigned in a 1:1 ratio to either the EA or the sham EA group. An independent statistician will generate the randomization sequence using SPSS software (version 26.0; IBM Corp., Armonk, NY, USA), employing a simple randomization procedure. The allocation sequence will be concealed using sequentially numbered, opaque, sealed envelopes (SNOSE) until baseline assessments are completed and the participant is assigned to a treatment group (27, 28).

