To minimize bias from participant dropout, we have preemptively developed comprehensive strategies, including offering flexible scheduling, allowing tolerant visit time windows, enhancing communication with participants, establishing an early warning system for dropouts, and strictly applying the intention-to-treat (ITT) principle in data analysis, combined with multiple imputation methods to handle missing data. Finally, for ethical considerations, participants can continue any pre-existing specialized SUI treatments; however, all such concomitant treatments will be meticulously recorded and considered as covariates in the statistical analysis to control for their potential confounding effects.

Several other limitations of this study should be acknowledged. First, the single-center design and recruitment of participants from a single institution may limit the sample representativeness and generalizability of the findings. Consequently, the external validity and generalizability of the conclusions may be limited and should be interpreted cautiously. Differences in healthcare settings and patient populations across regions may affect the widespread applicability of the findings. Although unified operator training was implemented to standardize the protocol, other single-center factors, such as the specific treatment environment and equipment, could introduce systematic bias. Second, although the sample size meets the basic requirements for the primary outcome, it is relatively modest compared to large multicenter trials (7). The relatively small sample size may reduce the statistical power for detecting significant effects in exploratory subgroup analyses and some secondary outcome measures. Third, as SUI is a chronic condition, understanding long-term outcomes is crucial. However, this study is limited to assessing short-term efficacy immediately post-intervention due to budgetary and logistical constraints. The lack of follow-up beyond 6 weeks precludes conclusions regarding the sustainability of treatment effects and the long-term efficacy of electroacupuncture. To address these limitations, future research should prioritize multicenter, large-sample randomized controlled trials that enroll more diverse populations and incorporate long-term follow-up (e.g., ≥6 months). Such studies are needed to comprehensively evaluate electroacupuncture's efficacy and sustainability for SUI and generate more robust evidence to guide its clinical application.

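### The primary comparison of change in pad weight makes no use of the baseline pad weight; ANCOVA would be more precise at the same sample size

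*Protocol article*

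**What the plan says.** - **Outcome.** The Primary outcome section (2.5.1) defines it as "The change in urine leakage, as measured by the 1-hour pad test, from baseline to week 6". Table 1 schedules the measurement at week 0 and week 6 only.
- **Test.** Statistical methods (2.6.4) gives one rule for continuous data: "Comparisons of continuous variables between the two groups will be performed using the independent samples" t-test when data are normal, Mann-Whitney otherwise. The significance criterion is that "a two-sided *P* value of less than 0.05 will be considered statistically significant".
- **Design basis.** Sample size calculation (2.6.1) matches that test: "The sample size was calculated for a superiority trial comparing two independent means". The inputs are mean changes of 8.59 g and 4.81 g with a standard deviation of 4.76 g.
- **Other models.** Section 2.6.4 adds: "For longitudinal analysis of outcomes measured over time, generalized estimating equations (GEE) or linear mixed-effects models will be employed", with interest in the time-by-group interaction. It does not say how baseline enters these models.
- **Covariates.** The only ones named are in the Discussion, on concurrent treatment for incontinence: "all such concomitant treatments will be meticulously recorded and considered as covariates in the statistical analysis". Baseline leakage is not among them.
- **Randomisation.** Section 2.6.2 uses simple randomisation without stratification. Allocation is concealed "until baseline assessments are completed and the participant is assigned to a treatment group", so the baseline pad weight exists before the arm is revealed.

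**The concern.** A woman cannot improve by more than she leaked at baseline, so the change is likely to depend on the baseline value. An unadjusted test of change treats that predictable part as noise. Adjusting for baseline removes it, which narrows the confidence interval and raises power from the same participants.

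Simple randomisation of 64 women also leaves room for the arms to differ in baseline leakage by chance. The arm that starts higher will then tend to show a larger fall through regression to the mean, and an unadjusted comparison of change does not correct for this.

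At stake is the precision of the primary estimate in a trial whose Discussion itself calls the sample modest.

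**Working it through.** **1. Reproduce the plan's sample size (2.6.1).** The difference is 8.59 − 4.81 = 3.78 g and the SD of change is 4.76 g.

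n = 2 × (1.96 + 0.84)² × 4.76² / 3.78² = 24.86, so 25 per arm. Then 25 / 0.8 = 31.25, so 32 per arm and 64 in total. Both figures reproduce.

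**2. Power of the planned t-test.** The noncentrality at 25 per arm is 3.78 / (4.76 × √(2/25)) = 2.81. Power is 80.2% by the plan's normal approximation and 78.6% by the noncentral t. At 32 per arm it is 88.8% and 87.8%.

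**3. Effect of adjusting for baseline.** Let c be the correlation between baseline and change. ANCOVA reduces the residual SD to 4.76 × √(1 − c²). If baseline and week-6 variances are equal and ρ is the baseline to week-6 correlation, then 1 − c² = (1 + ρ)/2. The protocol gives neither c nor ρ, so a range is shown. Power is by the noncentral t.

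| Assumed ρ | Residual SD (g) | Power, 25 per arm | Power, 32 per arm | 95% CI half-width, 25 per arm (g) | CI narrowing, 1 − √((1 + ρ)/2) | Evaluable n per arm for 80% power (normal approx.) |
|---|---|---|---|---|---|---|
| Unadjusted | 4.76 | 78.6% | 87.8% | 2.71 | – | 25 |
| 0.3 | 3.84 | 92.7% | 97.2% | 2.18 | 19% | 17 |
| 0.5 | 4.12 | 88.8% | 95.0% | 2.35 | 13% | 19 |
| 0.7 | 4.39 | 84.7% | 92.4% | 2.50 | 8% | 22 |
| 0.9 | 4.64 | 80.5% | 89.4% | 2.64 | 3% | 24 |

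**4. Simulation check.** With 10,000 runs per ρ at 25 per arm, unadjusted against ANCOVA gave 78.8% against 92.5% (ρ 0.3), 78.5% against 87.8% (0.5), 78.5% against 84.3% (0.7) and 78.7% against 79.6% (0.9). The ANCOVA figures lie up to one point below the table.

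**5. Without equal variances.** The gain then depends on c directly. For c = 0.2, 0.4 or 0.6, noncentral-t power at 25 per arm is 80.1%, 85.1% or 93.0%. If the slope of week 6 on baseline is exactly 1, then c = 0 and nothing is gained. One such case is ρ = 0.8 with a week-6 SD 1.25 times the baseline SD (0.8 × 1.25 = 1).

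**6. Size of a chance imbalance.** With equal variances and ρ = 0.5, the baseline SD is 4.76 / √(2 × 0.5) = 4.76 g. With 32 per arm, the standard error of the baseline difference is 4.76 × √(2/32) = 1.19 g. An imbalance of one standard error shifts the difference in mean change by (1 − 0.5) × 1.19 = 0.6 g, or 16% of 3.78 g.

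**7. Whether the GEE or mixed model already solves this.** The pad test has two time points. With baseline as an unconstrained response and complete data, the time-by-group term equals the difference in mean change, so it recovers nothing. A model that forces equal baseline means would recover the precision, but none is described.

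**The case against.** The strongest case against is that nothing in the plan is wrong. The outcome is a change, the trial is sized for two mean changes, the test compares two mean changes, and the sample size reproduces. All of that stands.

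A reader might infer stronger claims that the protocol does not support:

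- **That the primary result would be biased.** Under randomisation the unadjusted comparison is unbiased with the right type I error. Chance imbalance is random error already covered by the standard error. The shift in step 6 is conditional on an imbalance that may not occur.
- **That the trial is underpowered.** By its own formula it has 80.2% at 25 per arm. The 78.6% reflects the t rather than the normal distribution and assumes the full 20% dropout. With all 32 per arm the figure is 87.8%.
- **That adjustment helps at any correlation below 1.** This needs equal variances. The gain can be zero (step 5), and it is slight at ρ = 0.9.

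Two further objections carry some weight. First, the 2.6.4 rule is generic and does not name the primary outcome, and an unseen analysis plan might add covariates. Even so, the outcome definition, the sample size basis and the stated tests all point to an unadjusted comparison, and the one covariate statement leaves baseline leakage out. Second, a floor at zero leakage may make the relation non-linear and the variances unequal. The table is therefore illustrative, covers only the t-test branch, and a plain ANCOVA needs a provision for skewed residuals.

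**Conclusion.** The concern holds as a matter of efficiency, not validity. The stated primary comparison ignores a baseline value that is collected in everyone. Under the plan's own effect and SD, equal variances and 25 per arm, the cost is about 14, 10, 6 or 2 percentage points of power at ρ = 0.3, 0.5, 0.7 or 0.9. The gain is worthwhile at moderate correlations and small at high ones. Because the protocol does not report the correlation, no single figure can be claimed. Since the remedy costs almost nothing, it is worth adopting across that range.

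**What to change.** - **Primary analysis.** Prespecify ANCOVA of week-6 1-hour pad weight (or its change) on treatment arm and baseline pad weight, in the multiply imputed intention-to-treat data. Report the adjusted mean difference with its 95% confidence interval.
- **Skewness.** In place of the switch to Mann-Whitney, name a sensitivity analysis for skewed residuals: a transformation, robust standard errors or rank-based ANCOVA.
- **Other outcomes.** Apply the same adjustment to the continuous sEMG and ultrasound measures. It does not apply to urethral funnelling or cystocele type, which are categorical. For IEF and ICIQ-SF, measured at weeks 2, 4 and 6, keep the GEE or mixed model and include the baseline value as a covariate.

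The cost is a change of wording before unblinding. The baseline values are already collected, SPSS fits the model, and the sample size stays at 64.

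### The observed distribution decides whether the primary pad-test change is compared by means or by ranks, and on the rank branch the plan names no estimate, pooling quantity or matching interval

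*Protocol article*

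**What the plan says.** Section 2.5.1 defines the primary outcome as "The change in urine leakage, as measured by the 1-hour pad test, from baseline to week 6". Table 1 schedules the pad test at week 0 and week 6 only.

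Section 2.6.4 (Statistical methods) sets one rule for two-group comparisons of continuous variables: an independent-samples t-test ("for normal data) or the Mann–Whitney" U-test when they are not normal). The summaries follow the same split. Normal variables are given as mean and SD, "while those with a non-normal distribution will be summarized as median and interquartile range (IQR"). No criterion for normality is stated, and the primary outcome has no separate test or effect measure.

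The same section says of the intention-to-treat analysis that "missing data will be handled using multiple imputation by chained equations (MICE"). It adds that "Results will be presented with 95% confidence intervals" and that a two-sided P "value of less than 0.05 will be considered statistically significant".

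Section 2.6.1 reads: "The sample size was calculated for a superiority trial comparing two independent means". It assumes mean changes of 8.59 g and 4.81 g and a common SD of 4.76 g.

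**The concern.** Three parts of the plan fit the t-test branch and not the other.

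- **The hypothesis.** The trial is sized on a difference in mean grams. Unless the two distributions differ only by a shift, Mann-Whitney does not test a difference in means. The outcome data would then choose the effect measure.
- **The imputation.** Rubin's rules combine an estimate and its variance from each imputed data set. A Mann-Whitney U or P value is neither, and the plan names no estimator to go with it.
- **The interval.** A 95% confidence interval for a mean difference can disagree with a Mann-Whitney P value. The plan names no interval that belongs to the rank test, and the medians and IQRs it would report describe each arm, not the contrast.

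At stake is whether the headline P value, estimate and interval all refer to the same quantity, and whether that quantity is the one the trial was designed to detect.

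**Working it through.** **Step 1: reproduce the plan's own figure.** Inputs from section 2.6.1: difference 8.59 − 4.81 = 3.78 g, SD 4.76 g, z-values 1.96 and 0.84, margin 0.

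n = 2 × (1.96 + 0.84)² × 4.76² / 3.78² = 2 × 7.84 × 22.6576 / 14.2884 = 24.86, so 25 per group. With 20% dropout, 25 / 0.80 = 31.25, so 32 per group and 64 in total. The stated figures reproduce exactly, and they are figures for a comparison of means.

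Power for the mean difference:

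| n per group | z formula | exact t-test |
|---|---|---|
| 25 | 80.2% | 78.6% |
| 32 | 88.8% | 87.8% |

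**Step 2: how often the written rule leaves the t-test.** Simulation at 25 per arm. The following are assumptions, not in the protocol: Shapiro-Wilk P < 0.05 in either arm triggers Mann-Whitney, and non-normal data are gamma-shaped.

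| Skewness | Switch to Mann-Whitney |
|---|---|
| 0 (normal) | 10% |
| 0.5 | 23% |
| 1 | 61% |
| 1.5 | 91% |

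Repeat runs agreed within about one percentage point.

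**Step 3: does the choice of branch matter?** Under the planned 3.78 g shift with SD 4.76 g (20,000 runs per scenario), the two tests disagree on significance in 6.1% of trials with normal data. For gamma shapes 4, 2 and 1 they disagree in 7.8%, 10.7% and 15.1%. Gamma skewness is 2/√shape, so these shapes have skewness 1, 1.41 and 2.

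**Step 4: type I error of the rule.**

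- Identical distributions in both arms: 5.0% to 5.2% over the normal and three gamma cases. A further check at skewness 0 to 1.5 gave about 5% to 6%.
- Equal means, EA-arm SD 1.5 times larger: the rule rejects in 6.9%, 8.7% and 13.4% (skewness 1, 1.41 and 2), against 5.2% to 5.5% for the t-test.
- Equal means, skewness 1.5: Mann-Whitney rejects in about 9% to 10% at SD ratio 1.5 and 13% to 14% at SD ratio 2 across independent runs, against about 5% to 6% for the Welch test. The rule uses Mann-Whitney in about 91% of trials at this skewness, so the rule as a whole behaves much the same.
- Equal means, opposite skew in the two arms: 8.4% to 20.9% for the rule, 5.2% to 6.5% for the t-test.

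The rise therefore needs the arms to differ in spread or shape. In those cases Mann-Whitney is not malfunctioning. It is answering a question other than the one about means.

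**Step 5: the branches side by side.**

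| | t-test branch | Mann-Whitney branch |
|---|---|---|
| Effect measure | difference in means (g) | none named |
| Quantity for Rubin's rules | difference and its standard error | none named |
| Matching 95% interval | for the mean difference | none named |
| Match with section 2.6.1 | yes | no |

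**The case against.** *The primary hypothesis is defined.* A reader might infer that the switch leaves it undefined. That goes too far: section 2.6.1 frames superiority as a difference of two means with margin 0, and section 2.5.1 fixes the outcome. What is left to the data is the effect measure actually tested.

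*The analysis can be done.* A reader might also infer that the intention-to-treat analysis is impossible on the rank branch. It is not. Inverting the Mann-Whitney test gives the Hodges-Lehmann shift with an interval in grams, and an approximate standard error could be pooled. The narrower point stands: neither that estimator nor a pooling rule is named. Nor does the protocol say that normality would be judged separately in each imputed data set, so it cannot be asserted that the test would change from one set to the next. One judgement on observed data is equally compatible with the text.

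*Details belong in the analysis plan.* Normality criteria and pooling mechanics are indeed commonly left there, and their absence is no fault. The switch itself, however, is a rule that the article states.

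*The mixed-model sentence may cover the primary outcome.* Section 2.6.4 assigns generalized estimating equations or mixed models to repeatedly measured outcomes, and the Discussion promises covariates for concomitant treatments, which neither two-sample test can carry. But the primary outcome is a single change score from two time points, so that sentence does not clearly apply. If it did, the primary analysis would have more candidates, not fewer.

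*Analysts are blinded* (section 2.6.3). This limits steering towards one arm, but the choice still depends on the data.

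*The rule does little harm to error rates or power.* Largely true. Error is near nominal for identical distributions. Under a pure shift the rule's power was 78.6% with normal data and 82.6% to 93.6% with gamma data, against about 79% for the t-test throughout. Nothing in the protocol supports the skewness and SD ratios behind the larger error rates, and section 2.6.1 uses one common SD.

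**Conclusion.** The point holds in a limited form. As written, the distribution of the trial's own data decides whether the primary comparison is of means or of ranks. The rank branch does not match the sample-size hypothesis and comes with no named estimate, standard error to pool, or interval.

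The size is moderate. How often the switch occurs depends on skewness, which the protocol does not report: from about 10% of trials with normal data to about 91% at skewness 1.5, given Shapiro-Wilk at 5% in each arm. A reader might take the 10% to 13% rejection rate as the trial's false-positive risk. The documents do not support that. It arises with equal means under an assumed skewness of 1.5 and SD ratio of 1.5 to 2, whereas identical distributions give about 5% to 6%. The reason to act is an effect measure that is not fixed in advance and a test that may not agree with its reported interval.

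**What to change.** For the primary outcome, delete the normality switch in section 2.6.4 and name one analysis:

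- **Effect measure:** the between-group difference in mean pad-test change from baseline to week 6, in grams.
- **Model:** linear model with treatment group and baseline pad weight (analysis of covariance). With baseline in the model, the treatment estimate is the same whether week-6 weight or week 6 minus baseline is the response: subtracting baseline lowers only the baseline coefficient by 1. If change is expressed as a reduction, the sign reverses and nothing else.
- **Standard errors:** heteroscedasticity-robust with a small-sample correction, for example HC3 with a t reference. The uncorrected form with a normal reference rejected in about 6% of null trials at 25 per arm.
- **Imputation:** fit the model in each imputed data set and pool by Rubin's rules, reporting the pooled difference, its 95% confidence interval and P value.
- **Sensitivity analysis:** a rank-based test on observed cases, named as such.

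The model can also carry the concomitant-treatment covariates mentioned in the Discussion, if the plan keeps them.

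The cost is a short change to the analysis text. The sample size stays at 25 evaluable per group and 64 in total. The downside is some loss of power relative to a rank test if the tails are very heavy; the sensitivity analysis would show this. Fixing Mann-Whitney instead would need its own estimator and sizing: with normal data and a relative efficiency of 0.955, 25 / 0.955 = 26.2, so about 27 per group.

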#### Secondary outcomes

2.5.2

Incontinence episode frequency (IEF): Mean IEF over 72 h will be recorded in a bladder diary. Assessments will be performed at baseline, week 2, week 4, and week 6. Change from baseline will be calculated.ICIQ-SF score: The International Consultation on Incontinence Questionnaire-Short Form (ICIQ-SF) will be used to retrospectively evaluate the frequency, volume of Incontinence, and impact on quality of life over the preceding four weeks. The validated Chinese version will be administered (22). The questionnaire includes three scored items (assessing the frequency of urinary Incontinence, the amount of leakage, and the degree of interference with quality of life) and one non-scored self-diagnosis item (used to provide additional qualitative information). The total score ranges from 0 to 21, with higher scores indicating greater symptom severity (23). Scores will be collected at baseline, week 2, week 4, and week 6.Severity of SUI: The overall severity of urinary leakage was evaluated based on patient-recorded 72-hour bladder diaries, which documented episodes occurring under normal circumstances (i.e., excluding vigorous coughing, exercise, or heavy lifting). Severity was categorized as follows: Mild: leakage of a few drops; Moderate: leakage that partially soaks a pad; Severe: leakage that thoroughly soaks a pad in a single episode. The most severe episode encountered is recorded (7). To enhance objectivity, all participants will be provided with standardized urinary pads (Brand: TENA, Size: 375 mm × 135 mm, Absorption: 100 mL). Additionally, we will record the 72-hour cumulative pad weight (difference between wet and dry weight using a precision scale  ± 0.1 g) as a quantitative measure of leakage severity. Participants can store pads in labelled zipper bags for weighing, reporting daily and 72-hour total leakage amounts. The severity of stress urinary incontinence will be assessed by trained outcome assessors who are blinded to the participants' group allocation. Assessments will be conducted at baseline, week 2, week 4, and week 6.Weekly usage of urine pads: Participants will maintain a daily diary to record the number of pads used. The change from baseline in the average number of pads used per 2 weeks will be calculated. To provide objective supplementation, we will also derive two metrics from standardized pad weights: weekly total pad weight (g) and mean leakage per pad (g/pad). Provide participants with identical pads and labeled bags. Each pad's dry weight should be pre-measured and labeled at the center (ID and tare), with participants returning only the wet pads. All weighings should be performed on the same scale, by the same trained personnel, within a fixed time window, with daily calibration logs maintained. Data will be collected at baseline, week 2, week 4, and week 6.Participants' self-evaluation of therapeutic effects: This subjective satisfaction rating assesses participants’ perception of treatment benefit. Participants will be asked, “Has the treatment helped you control your urine leakage?” Responses will be rated on a 4-point scale: 0 = not helpful at all; 1 = slightly helpful; 2 = moderately helpful; 3 = very helpful (7). Evaluations will be performed at week 2, week 4, and week 6.Pelvic floor muscle surface EMG (sEMG): Parameters will be assessed at baseline and week 6 using the standard Glazer protocol with participants in the lithotomy position (24). The evaluated parameters include: pre-resting baseline tone; amplitude of phasic (Type II fast-twitch) muscle contractions (calculated as the mean amplitude of five rapid contractions); amplitude of tonic (Type I slow-twitch) muscle contractions (calculated as the mean amplitude of five 10-second sustained contractions); endurance of Type I muscles (mean amplitude during a single 60-second sustained contraction); and post-resting baseline tone. Changes in the EMG amplitude for both Type I and Type II muscle fibers from baseline to week 6 will be analyzed.Transperineal ultrasound (TPUS): TPUS assessments will be performed at baseline and week 6 with participants in the lithotomy position. Parameters to be measured include: bladder neck mobility, urethral rotation angle, retrovesical angle (posterior bladder angle), position of the lowest point of the bladder (bladder neck descent), urethral funneling, and the type of cystocele (bladder prolapse) at rest and during the Valsalva maneuver (25).Evaluation of discomfort during treatment: Discomfort experienced during the acupuncture session will be evaluated using a Visual Analog Scale (VAS) ranging from 0 cm (indicating no discomfort) to 10 cm (indicating severe discomfort). The average VAS score recorded within 5 min after the first and ninth treatments will be used for analysis. If a score from one session is missing, the available score from the other session will be used (7).Participants' acceptability evaluation: The acceptability of the treatment procedure will be rated on a 5-point scale: 0 = very difficult to accept; 1 = somewhat difficult to accept; 2 = acceptable; 3 = easy to accept; 4 = very easy to accept. The average score will be calculated within 5 min after the first and ninth treatments. If a score from one session is unavailable, the score from the remaining session will be utilized (7).

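### The plan names no ordinal method for two ordered secondary outcomes, so on a plain reading they get tests that ignore order and give no single effect estimate

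*Protocol article*

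**What the plan says.** Statistical methods (2.6.4) sorts between-group comparisons into two branches. Continuous variables get a t-test if normal and a Mann–Whitney test if not. For the rest: "Categorical data will be described as frequencies and percentages, and comparisons between groups will be made using the appropriate Chi-squared test" or Fisher's exact test. A two-sided P "value of less than 0.05 will be considered statistically significant". A further sentence covers outcomes measured over time, by GEE or linear mixed-effects models, with no link function named. The section also says that results come with 95% confidence intervals, and that secondary outcomes, which it calls exploratory, will be read through effect sizes and intervals more than through P values.

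Secondary outcomes (2.5.2) defines two outcomes on ordered categories:
- SUI severity: "Mild: leakage of a few drops; Moderate: leakage that partially soaks a pad", with a third grade, severe, for a thoroughly soaked pad. It is assessed at baseline and weeks 2, 4 and 6.
- Self-evaluated benefit: "Responses will be rated on a 4-point scale: 0 = not helpful at all", rising to 3 for very helpful. It is assessed at weeks 2, 4 and 6.

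**The concern.** Both scales have a natural order, and neither branch of the plan uses it. A Pearson chi-squared or Fisher test on a 2×3 or 2×4 table treats any rearrangement of the categories as equal evidence. It spreads its power over two or three degrees of freedom and produces a P value with no direction and no single between-arm estimate.

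Two things are at stake. First, the named test cannot deliver what the same section promises for secondary outcomes, an effect size with an interval. This needs no assumption about the size of the effect. Second, power is lost in a 64-patient trial whose Discussion already concedes limited power for some secondary outcomes. The repeated-measures sentence does not close the gap: a linear mixed model would treat the grades as equally spaced numbers, and GEE uses the ordering as such only if an ordinal link is chosen.

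**Working it through.** **1. The plan's own figure.** The only sample-size calculation is for the primary outcome. Inputs from Sample size calculation (2.6.1): "a two-sided *α* of 0.05" (Z = 1.96), 80% power (Z = 0.84), "EA group mean *μ_t_* = 8.59 g", "Sham EA group mean *μ_c_* = 4.81 g", "standard deviation *σ* = 4.76 g", margin 0.

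n = 2(1.96 + 0.84)² × 4.76² / (8.59 − 4.81)² = 2 × 7.84 × 22.66 / 14.29 = 24.86, so 25 per group. 25 / 0.80 = 31.25, so 32 per group and 64 in total. The stated figure reproduces. I use 32 per arm (all randomised) and 25 per arm (after the planned dropout).

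**2. Degrees of freedom.** Take a one-degree-of-freedom ordered test with noncentrality λ and put the same λ into a chi-squared test on k − 1 degrees of freedom, α = 0.05:

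| Ordered test power | λ | 3 categories (2 df) | 4 categories (3 df) | Loss (points) |
|---|---|---|---|---|
| 50% | 3.84 | 40.1% | 34.5% | 9.9 / 15.5 |
| 60% | 4.90 | 49.5% | 43.2% | 10.5 / 16.8 |
| 70% | 6.17 | 59.7% | 53.1% | 10.3 / 16.9 |
| 80% | 7.85 | 70.9% | 64.5% | 9.1 / 15.5 |

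**3. Simulation at the trial's size.** The document gives no category distribution and no odds ratio for either outcome, so both are assumptions. Each scenario has 20,000 runs: Pearson chi-squared against Mann–Whitney with tie correction. Each cumulative odds in the sham arm is divided or multiplied by a common odds ratio (OR) to give the EA arm, always in the direction of benefit.

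- Benefit, four equal sham levels: cumulative odds 1/3, 1, 3. At OR 3 these become 1/9, 1/3, 1, so EA is .10/.15/.25/.50.
- Severity, sham .50/.40/.10 for mild/moderate/severe: cumulative odds 1, 9. At OR 3 these become 3, 27, so EA is .75/.214/.036.

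Power at 32 per arm, chi-squared against Mann–Whitney:

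| OR | Benefit, 4 levels | Loss (points) | Severity, 3 grades | Loss (points) |
|---|---|---|---|---|
| 1.5 | 10.1% v 14.6% | about 4 | 9.9% v 13.3% | about 3 |
| 2 | 21.2% v 32.4% | about 11 | 21.2% v 28.8% | about 8 |
| 3 | 48.6% v 66.2% | about 18 | 44.4% v 56.5% | about 12 |
| 4 | 69.5% v 84.5% | about 15 | 62.1% v 73.7% | about 12 |
| 6 | 89.5% v 96.4% | about 7 | 81.6% v 89.3% | about 8 |

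Across the other control distributions tried, the loss at OR 1.5 is about 2–5 points. The peak at 32 per arm lies near OR 2.5–3: about 10–12 points for three grades and 16–19 for four levels. At 25 per arm the peak is of the same height but sits at OR 3–4. Fisher's exact test gives losses of similar size.

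**4. If severe is rare.** Entry is restricted to mild or moderate SUI (section 2.2), so few participants may be graded severe. At OR 3 and 32 per arm, with the rest of the sham arm split about equally between mild and moderate:
- 4% severe in sham: 44.5% v 54.6%, about 10 points.
- 2%: 48.5% v 55.7%, about 7 points.
- 1%: 50.8% v 55.5%, about 5 points, because the scale is then nearly binary.

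**5. Type I error.** With OR 1, rejection rates are about 4–5% for chi-squared and about 5% for Mann–Whitney (up to about 6% in the sparsest tables). Nothing is inflated by the planned test.

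**The case against.** The strongest reply is that the article never assigns either outcome to chi-squared or Fisher by name. The sentence is generic, the word appropriate does not rule out a trend version, and both outcomes are repeated, so the GEE sentence may cover them with a cumulative-logit link. Mapping outcomes to tests and choosing a link are often left to an analysis plan, and this is a condensed article. That stands as far as it goes: a reader who infers that the trial has committed these two outcomes to chi-squared goes beyond the text. But the article did choose a test family for categorical data and did confine the rank test to continuous data, and no sentence in it points to an ordinal method.

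A reader might also infer a fixed loss of 10 to 17 points. The document does not support that. Those values sit near the maximum and depend on an odds ratio and category distributions that it does not give.

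Nor does it follow that direction would be unknown. The planned frequencies and percentages would show it informally, and severity has a quantitative companion in the 72-hour pad weight. What would be missing is one between-arm estimate on the ordered scale with its interval.

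Finally, these outcomes are exploratory and P values are played down. That lowers the weight of the power argument, but raises that of the missing estimate.

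**Conclusion.** The point holds as a minor one. The methods section names no analysis that respects order for SUI severity or self-rated benefit, and the default it states does not yield the effect size and interval on which it says these outcomes will be judged. The price is precision in two secondary outcomes. The primary analysis, its sample size and the type I error are untouched.

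The amount is conditional on proportional odds, 25–32 per arm and assumed category distributions: about 2–5 points of power at OR 1.5, and at most about 10–12 points (three grades) or 17–19 points (four levels) at moderate odds ratios. It is smaller again at large effects, or if severe is hardly used.

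**What to change.** Add to Statistical methods that severity and self-evaluation will be analysed with an ordinal method. This would be a proportional-odds model at week 6, or GEE with a cumulative-logit link across visits, reporting a common odds ratio with its 95% interval and adjusting severity for its baseline grade. Name the Mann–Whitney test as fallback if categories are too sparse or the model does not fit. Keep chi-squared and Fisher for nominal and binary items, such as urethral funneling, cystocele type and the occurrence of adverse events.

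This changes wording only, needs no new data and should be settled before unblinding. There is a small downside: the model assumes proportional odds and may be unstable with sparse categories at 32 per arm, which is why the fallback should be stated in advance.
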